##### Amount of time counted as moderate to vigorous physical activity (MVPA)

*Inactive* less than 150 min per week engaging in moderate-intensity physical activity and less than 75 min per week engaging in vigorous-intensity physical activity*Active* 150 min or more per week engaging in moderate-intensity physical activity or 75 min or more per week engaging in vigorous-intensity physical activity

#### Study outcomes

##### 3.1.6.1. Primary outcome measures: clinical outcomes listed below will be gathered at the participant’s first visit (baseline) and at 6- and 12-month post-treatment.

Amount of physical activity and sleep duration objectively measured using ActiGraph wGT3X-BT (ActiGraph, Florida, USA), a validated 3-axis accelerometer that includes ambient light sensors. Actigraphy is a method to monitor the cycles of rest and activity, which does not involve any invasive procedures. The movements of the accelerometer and light exposure can be continually recorded with a watch-like device worn on the wrist to objectively determine the amount of physical activity and sleep duration of a participant. Despite its limitations in measuring and staging sleep, actigraphy data provides real-life information on both the objective amount of physical activity and sleep by allowing the participant to maintain normal routines in his or her natural environment. Physical activity is measured at baseline only. (Fig. 1)*Amount of comfortable mouth opening* [12] the participant will be asked to open his or her mouth as wide as possible while remaining pain-free. If the participant is already experiencing pain, open as wide as possible without increasing current pain. Interincisal distance between the maxillary and mandibular reference teeth will be measured.*Amount of maximum mouth opening* [12] the participant will be asked to open as wide as possible, even if it is painful. Interincisal distance between the maxillary and mandibular reference teeth will be measured.*Muscle tenderness on palpation* [12] 12 masticatory muscle areas will be palpated on both sides including posterior, middle, and inferior temporalis muscle area and origin, body, and insertion of the masseter muscle with 1 kg of pressure.*Joint capsule tenderness on palpation* [12] 6 areas of TMJ will be palpated on both sides including the posterior, superior, and lateral parts of the capsule with 0.5 kg of pressure in a passive state. When palpation elicits subjective pain, the response will be recorded as positive. Joint noises are verified through palpation.*Subjective pain intensity* participant reported pain intensity based on a 0–10 numeric rating scale (NRS).

**Fig. 1 Fig1:**
[figure not shown]
Wrist worn accelerometer

##### Secondary outcomes: comorbidity and systemic inflammation levels

Series of validated structured questionnaires to assess comorbidity levels (Table 1)Hematologic indices of systemic inflammation: red blood cell (RBC) levels showed significant correlations with pain intensity before treatment, comfortable mouth opening, pain on palpation of cervical muscles, and mouth opening range at 6 months after treatment [33]; hsCRP and erythrocyte sedimentation rate (ESR) are non-specific markers of inflammatory activity used in patients of rheumatoid arthritis or spondyloarthritis [34]; platelet-to-lymphocyte ratio (PLR), neutrophil–lymphocyte ratio (NLR), and derived neutrophil–lymphocyte ratio (dNLR) are widely used inflammatory biomarkers showing significant correlation with disease activity and mortality [35–38].

**Table 1 Tab1:** List of structured questionnaires to measure comorbidities

Section	Questionnaire	Description
Physical activity	International physical activity questionnaire (IPAQ) [13]	assess physical activity level based on self-report
	Tampa scale of kinesiophobia for temporomandibular disorders (TSK-TMD) [14, 15]	assess the severity of exaggerated, incoherent, and debilitating fear of movement and activity
Sleep disturbance and fatigue	Pittsburgh sleep quality index (PSQI) [16]	assess the quality of sleep over a one-month period
	Epworth sleepiness scale (ESS) [17]	assess the daytime sleepiness of the patients
	Fatigue assessment instrument (FAI) [18]	assess fatigue and distinguish normal fatigue from fatigue-related medical disorders
	Insomnia severity index (ISI) [19]	assess the severity of insomnia
	Morningness−eveningness questionnaire (MEQ) [20]	investigate morningness and eveningness of patients as to when the subject would prefer to start sleep or wake up, rather than when he or she actually does
Widespread pain	Symptom severity (SS) scale [21]	diagnose fibromyalgia in patients based on the adapted 2010 American College of Rheumatology fibromyalgia survey criteria. And also, to assess the severity of widespread body pain and centralized pain characteristics
	Widespread pain index (WPI) [21]	
	Fibromyalgia impact questionnaire (FIQ) [22]	measure status, progress and outcomes of fibromyalgia-like widespread pain by assessing physical performance, work condition, depression, anxiety, tiredness in the morning, pain, rigidity, fatigue, and well-being over the one-week period
Psychologic disturbance	Symptom checklist-90-revised (SCL-90-R) [23]	evaluate psychological problems and psychotic symptoms
	Beck depression index (BDI) [24]	evaluate presence of pathological levels of depression over the recent one-week period
	Beck anxiety index (BAI) [25]	assess the severity of physical and cognitive symptoms originating in anxiety over the recent one-week period
	Pain catastrophizing scale (PCS) [26]	assess the patient’s tendency to exaggerate the threat of a pain stimulus and to feel helpless
	Central sensitization inventory (CSI) [27]	identify patients who have symptoms that may be related to central sensitization or central sensitivity syndromes
	Pennebaker Index of Limbic Languidness (PILL) [28]	measure an individual’s tendency to notice an array of physical symptoms and sensations
	Perceived stress scale (PSS) [29]	measure nonspecific perceived stress
General health	Short form 36 (SF-36) [30]	evaluate difficulties in various activities including physical, social, and usual role, bodily pain, mental health in general, vitality, and general perceptions of health
	Composite autonomic symptom score 31 (COMPASS 31) [31]	score autonomic symptom severity in domains including orthostatic intolerance, vasomotor, secretomotor, gastrointestinal, bladder, and pupillomotor
	Short form McGill pain questionnaire (MPQ) [32]	document the quality and intensity of pain experienced by the patient

The study flow is given in Fig. 2.

**Fig. 2 Fig2:**
[figure not shown]
Flowchart of study process

We hypothesized that physical activity level could influence the long-term prognosis of pain and clinical indices of TMD in addition to sleep duration and quality, and other comorbidities related to psychosocial aspects.

### Data management and availability

The medical record number of each participant will be gathered to search for the required data.

Clinical and surveyed information of each participant will be recorded on a secure server and paper print-outs. Then the necessary information will be documented in an Excel file, which can be utilized for statistical analyses. The participants will be assigned a consecutive number and the names will not be disclosed in compliance with the International Conference of Harmonization for Good Clinical Practice recommendations [39]. The fact that their obtained information will be confidentially stored in a computer with high security will be notified to all participants. The participants’ written consent will be stored by the principal investigator. All data will be confirmed and authenticated by a biostatistician at Seoul National University. Since this study is an observational study rather than a clinical trial study, a data monitoring committee is not required. The principal investigator is in charge of any interim analyses and cessation.

The data gathered in this study will not be able to be accessed publicly owing to ethical issues however, will be available upon reasonable request from the corresponding author.

### Sample size calculation

Sample size estimation for this study was based on the primary outcome of physical activity level measured in minutes and 77.8 min as between-group difference. A total of 214 participants (107 per group) will be needed based on analysis to reach the power of 90% with an alpha error of 0.05 and an estimated study dropout rate of 20%.

### Statistical analysis

The obtained data will be analyzed using SPSS Statistics ver. 26.0 software (IBM Co., Armonk, NY, USA). The significance level will be set to 0.05. To compare differences between groups, both parametric and nonparametric tests will be adopted accordingly. Descriptive statistics for clinical variables and comorbidity levels will be presented as mean with standard deviation, and median with lower and upper quartiles. Logistic regression will be used to investigate factors associated with a worse long-term prognosis of TMD in terms of pain and function. All potential confounders, including clinical indices of TMD symptoms measured before treatment, body mass index, blood pressure and pulse rate, scores reflecting psychosocial status, sleep quality, and hematologic indices will be included as independent variables along with actigraphy data such as the amount of energy consumption per day, metabolic equivalent of task, steps count, sleep time, wake after sleep onset, sleep efficiency, sleep fragment index, and movement index. Factors will be added first in order to make adjustments, after which will be discarded consecutively one at a time with the first being the one with the highest *p*-value. The cutoff point of confounders to be discarded will be set as *p* < 0.250. If the *p*-value is 0.250 ≤ *p* ≤ 0.300, the confounder will not be discarded if this affects the OR by more than 10% [40]. Receiver operating characteristic (ROC) curves will be analyzed to explore thresholds for potential biomarkers. Their prognostic values will also be assessed by using Kaplan–Meier curve and both univariate and multivariate COX regression models. If the estimated sample size is not reached, multiple imputation will be used for missing data. A single overall analysis result will be produced by combining multiple analysis results.

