##### Pain disability level evaluated with graded chronic pain scale (GCPS) of DC/TMD axis II

*Low disability TMD group* GCPS grade I and II (low disability-low intensity pain and low disability-high intensity pain, respectively).*High disability TMD group* GCPS grade III and IV (high disability-moderately limiting pain and high disability-severely limiting pain, respectively)

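### The only method given for comparing groups has no baseline term, so any such test used at 6 or 12 months would mix starting severity with prognosis

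*Protocol article*

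**What the plan says.** The Abstract says the data will be analysed by TMD pain severity and by physical activity level. Patient grouping then defines two splits.

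- **Disability.** The Low group is "GCPS grade I and II (low disability-low intensity pain and low disability-high intensity pain, respectively"; the High group is "GCPS grade III and IV (high disability-moderately limiting pain and high disability-severely limiting pain, respectively".
- **Activity.** Active and Inactive are separated by weekly minutes of moderate or vigorous activity.

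Under the primary outcome measures, the clinical outcomes (comfortable and maximum mouth opening, muscle and joint tenderness, NRS pain) "will be gathered at the participant’s first visit (baseline) and at 6- and 12-month post-treatment". Physical activity itself is measured at baseline only.

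The Statistical analysis section gives one sentence on comparing groups: "To compare differences between groups, both parametric and nonparametric tests will be adopted accordingly". It deals with prognosis separately: "Logistic regression will be used to investigate factors associated with a worse long-term prognosis of TMD in terms of pain and function". The independent variables of that model are described as "All potential confounders, including clinical indices of TMD symptoms measured before treatment, body mass index" and further items, together with actigraphy indices. They enter first, "after which will be discarded consecutively one at a time with the first being the one with the highest" p-value. Kaplan–Meier curves and Cox models are planned for the prognostic value of potential biomarkers.

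**The concern.** Neither grouping is randomised, so the groups may differ at the start on the very outcomes followed up. This is most likely for the disability split, because GCPS grade describes pain and its consequences at presentation. The Objectives section asks about long-term effect, response to treatment and even causation. Each of these concerns how patients fare given where they began.

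A plain test on 12-month NRS pain or mouth opening answers a different question: whether the groups differ at 12 months for any reason, including having differed at baseline. A group that starts worse can look as though it has a worse prognosis when patients with the same starting value do equally well in both groups. The article itself lists pre-treatment clinical indices among the potential confounders in its logistic model. Its sentence on group comparisons says nothing of the kind.

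**Working it through.** **What the text fixes and leaves open.**

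| Item | Group-comparison sentence | Logistic model |
|---|---|---|
| Outcome | not named | worse prognosis (categorical) |
| Visit | not named | long term |
| Exposure | groups, not named | actigraphy indices listed; Active/Inactive and Low/High groups not named |
| Baseline clinical indices | not mentioned | entered, then open to removal by p-value |

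So the logistic model adjusts for baseline at the outset, but it is not a comparison of these groups on the continuous or count outcomes, and nothing guarantees that the baseline term stays.

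**Inputs for the size.** Sample size calculation gives 107 per group and 20% dropout: 107 × 0.8 = 85.6, about 86 per group. Alpha is 0.05, taken as two-sided because the article does not say. The baseline gap *g* (in SD units) and the baseline-to-follow-up correlation rho are not given, so both are assumed. There is no stated figure on a clinical outcome to reproduce. The 214 participants were set on a 77.8-minute difference in activity, and no SD is shown.

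**Unadjusted follow-up test, equal prognosis given baseline.**

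- Expected follow-up difference = rho × *g*.
- Standard error = √(2/86) = 0.1525 SD.
- For *g* = 0.5 the differences are 0.15, 0.25 and 0.35 SD at rho 0.3, 0.5 and 0.7. Divided by 0.1525 these are 0.98, 1.64 and 2.30.
- Rejection probabilities come from the noncentral t distribution with 170 degrees of freedom.

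| Assumed gap | rho 0.3 | rho 0.5 | rho 0.7 |
|---|---|---|---|
| 0.2 SD | 7% | 10% | 15% |
| 0.5 SD | 16% | 37% | 63% |
| 0.8 SD | 35% | 74% | 95% |

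**The same gap under a different null.** Suppose instead that both groups change by the same mean amount.

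- The baseline-adjusted difference is then (1 − rho) × *g*.
- Its standard error is about √[(1 − rho²)(2/86)(1 + *g*²/4)].
- For *g* = 0.5 the differences are 0.35, 0.25 and 0.15 SD, with standard errors 0.150, 0.136 and 0.112. The ratios are 2.33, 1.84 and 1.34.
- ANCOVA rejects about 64%, 45% and 26% of the time.

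Equal prognosis given baseline and equal mean change are therefore different hypotheses when groups start apart, and the plan has to say which one it means.

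**Precision.** Baseline adjustment multiplies the residual variance by 1 − rho², that is 0.91, 0.75 or 0.51. This gain shrinks where group and baseline value are correlated, which is the case of interest here, so it is a secondary benefit.

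**The case against.** The strongest reply is that the group-comparison sentence names no outcome and no visit. The only between-group difference the article quantifies is in activity minutes. Those are measured once, at baseline, so there is no earlier value to adjust for and a plain test is suitable. Which test goes with which outcome is also detail that a condensed article may leave to a full protocol or SAP. This much stands: a reader might infer that the article states that 6- and 12-month outcomes will be compared without adjustment, and it does not state that. What remains is that group comparison is given a method, the method has no baseline term, and nothing confines it to baseline, while the Abstract and the grouping and outcome sections point to comparisons over follow-up.

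A reader might also infer that the plan ignores baseline when it judges prognosis. It does not. Prognosis is assigned to a logistic regression that enters pre-treatment clinical indices. The weakness there is narrower: the outcome is categorical, the two groupings are not named as exposures, and elimination can remove the baseline term.

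Nor is a large baseline pain gap built into the GCPS split. The cut is by disability, and the Low group explicitly includes high-intensity pain. Some difference is likely, but the article gives no size for it, and it documents no gap for Active versus Inactive.

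Finally, ANCOVA is not a neutral correction in observed groups, as the second calculation shows. That is a reason to name the estimand. It does not justify leaving the follow-up comparison unadjusted.

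**Conclusion.** The concern holds in this limited form: as written, the plan permits unadjusted tests of follow-up clinical outcomes between observed groups, and any such test would confound starting severity with prognosis. The range of about 16% to 63% rejection in place of 5% depends on an assumed 0.5 SD gap, rho of 0.3 to 0.7, equal groups of about 86, a two-sided test and equal prognosis given baseline. Gaps of 0.2 to 0.8 SD widen it to 7% to 95%. These figures show how large the problem could be and do not predict what this study will find. The plan should be changed, because the remedy is cheap and uses measurements already scheduled. If the tests were meant only to describe baseline, saying so removes the problem for them.

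**What to change.** In Statistical analysis, add text to this effect:

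1. Any comparison of a clinical outcome between the Active/Inactive or Low/High disability groups at 6 or 12 months uses a regression on group (ANCOVA, or a mixed model over both visits) that always keeps the baseline value of that same outcome. Tenderness counts and skewed outcomes use an ordinal, count or rank-based version.
2. The estimand is the difference at follow-up between patients in the two groups with the same baseline value.
3. In the logistic model for worse prognosis, the baseline value of the outcome concerned is exempt from elimination.
4. Unadjusted parametric and nonparametric tests are descriptive.

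The cost is a few sentences and no new data. Patients without a baseline value need a stated rule, and each outcome uses one more degree of freedom. Because the groups are not randomised, adjustment reduces confounding but does not guarantee its removal, and the report should say so.

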## Objectives

Therefore, the main objectives of this “Physical Activity in TMD (PAT)” study are,To assess the long-term effect of objective physical activity level and sleep duration on clinical characteristics in well-defined TMD patient groups.To analyze the impact of physical activity on treatment response to conventional TMD management approaches by determining the cut-off value for physical activity that affects treatment prognosis.To define the causal relationship between abnormal physical activity levels and sleep durations on chronic, high-intensity TMD pain, its comorbidities, and systemic inflammatory marker levels.

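### Psychosocial scores, sleep quality and blood markers are outcomes of activity in one section and confounders in another, so the single fully adjusted activity odds ratio cannot be read as the overall effect of activity

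*Protocol article*

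**What the plan says.** All references are to the protocol article.

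- **Objectives.** Objective 1 is "To assess the long-term effect of objective physical activity level and sleep duration on clinical characteristics in well-defined TMD patient groups". Objective 2 is "To analyze the impact of physical activity on treatment response to conventional TMD management approaches". Objective 3 seeks the "causal relationship between abnormal physical activity levels and sleep durations on chronic, high-intensity TMD pain, its comorbidities, and systemic inflammatory marker levels".
- **Outcomes.** The secondary outcomes section is headed "Secondary outcomes: comorbidity and systemic inflammation levels". It covers the questionnaires on sleep, mood and other comorbidity, and the hematologic indices.
- **Statistical analysis.** "Logistic regression will be used to investigate factors associated with a worse long-term prognosis of TMD in terms of pain and function". Among the potential confounders, "scores reflecting psychosocial status, sleep quality, and hematologic indices will be included as independent variables" together with the actigraphy data. Covariates are then removed one at a time by p-value around a threshold of 0.250. Those between 0.250 and 0.300 are kept if they change the odds ratio by more than 10%.
- **Timing.** For the exposure, "Physical activity is measured at baseline only". Among the covariates, only the TMD clinical indices are tied to the period before treatment. No timing is given for the psychosocial, sleep or hematologic covariates.

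**The concern.** The same families of variables have two roles. In Objective 3 and the secondary outcomes they are consequences of activity. In the prognosis model they are nuisance variables to be held constant while activity is assessed.

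If a variable lies on the path from activity to prognosis, holding it constant removes the part of the effect that runs through it. What remains is a direct effect. Objectives 1 and 2 speak of the effect and impact of activity without saying that sleep, mood or inflammation are held fixed.

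At stake is what a null adjusted result can mean. The Discussion intends the findings to support guidance on physical activity. An odds ratio near 1 could mean that activity does not matter, or that it works through variables that the model has held constant. With one adjusted model, a reader could not tell which.

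**Working it through.** **1. What the document says about each variable's role**

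- *Mediator or outcome role.* Objective 3 puts comorbidities and inflammatory markers downstream of activity. The Discussion reports longer sleep and better sleep efficiency after exercise, and says the literature generally links more activity to less systemic inflammation. It then says that activity, sleep quality and inflammation all influence TMD symptoms. Both links of a mediating path are present for sleep and inflammation.
- *Confounder role.* The Background names psychological status and sleep quality as well-known confounders and says that the influence of sleep must be controlled. The Discussion calls the activity–sleep relation bidirectional, reports that poor sleepers are less active, and notes reduced activity in depression.

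Sleep has support for both roles, mood mainly for confounding, and inflammation mainly for mediation (with some mixed results).

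**2. Can the selection rules sort the roles?** No. A mediator that strongly predicts prognosis has a small p-value and stays in. Removing a mediator also changes the activity odds ratio, just as removing a confounder does, so the 10% rule favours keeping both.

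**3. Is there a figure in the plan to reproduce?** No. The only computed figure is 214 participants, based on a 77.8-minute difference in activity. It implies nothing about an odds ratio for prognosis or a mediated share. Everything below is illustration under assumed values.

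**4. Large-sample illustration** (400,000 simulated records)

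Let X be activity and M a marker, both standardised, with correlation −b. Assume logit P(poor prognosis) = −0.8 − 0.3X + 0.5M.

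- *Mediator case:* M = −bX + √(1−b²)·e.
- *Confounder case:* X = −bM + √(1−b²)·e.

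In the mediator case the linear-predictor total is −0.3 − 0.5b. The share running through M is 0.5b/(0.3 + 0.5b), which is 0.05/0.35 = 14% at b = 0.1 and 0.25/0.55 = 45% at b = 0.5. The fitted logistic models gave:

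| Role of M | b | OR without M | OR with M | Share of log OR removed |
|---|---|---|---|---|
| Mediator | 0.1 | 0.72 | 0.74 | 10% |
| Mediator | 0.5 | 0.59 | 0.74 | 44% |
| Confounder | 0.1 | 0.72 | 0.74 | 9% |
| Confounder | 0.5 | 0.59 | 0.74 | 43% |

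The fitted shares differ a little from the hand values because the odds ratio without M averages over M. The two roles give nearly the same numbers. In the first, the adjusted odds ratio leaves out part of the effect. In the second, the unadjusted one is biased.

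**5. Illustration at the trial's size**

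Completers: 214 × 0.80 = 171. Assume that half are inactive, that the total odds ratio for poor prognosis is 2.5, and that inactivity shifts one mediator by 0.5 SD. With mediated share s, the direct log OR is (1−s)·ln 2.5 and the mediator's coefficient is s·ln 2.5/0.5.

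- *s = 50%:* direct OR = exp(0.5 × 0.916) = 1.58. The mediator's OR per SD is exp(0.916) = 2.5, which is strong. The median OR falls from about 2.2 to 1.6, and power from roughly 64–71% to 22–27%, depending on the assumed event rate.
- *s = 25%:* power falls from roughly 72–81% to 47–56%.
- *s = 10%:* the OR falls only from about 2.5 to 2.3.

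**The case against.** The case on the other side has several parts.

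- *The hypothesis.* The hypothesis stated after the flowchart is that activity influences prognosis in addition to sleep and comorbidity. That reads naturally as a contribution beyond those variables, which an adjusted model estimates. Neither Objective 1 nor 2 says total or direct. This stands: the fully adjusted model has a legitimate purpose and should stay.
- *Confounding.* The Background and Discussion give good reason to adjust for mood and sleep. This stands too. A reader might infer that the protocol itself places all these variables on the causal path, so that the planned odds ratio is pulled toward 1 and the covariates should go. The documents do not support that, because they describe both directions.
- *Timing.* A score can be a baseline covariate and a follow-up outcome without contradiction. This is correct, but the section does not restrict these covariates to baseline. Baseline values would reduce the problem without ending it: a baseline recording of habitual activity is concurrent with sleep, mood and blood values that may already reflect that activity.
- *Other analyses.* Group comparisons, ROC curves and univariate Cox models are also planned. So it would be too strong to say that nothing unadjusted is estimated. None of these, however, is described as an adjusted estimate of activity with the possible mediators left out.
- *The simulations.* They assume mediation and so cannot demonstrate harm. This stands.
- *A condensed article.* Extra models may sit in the full plan. But the section positively fixes the covariate families, their label and the selection rule, and the point concerns that stated choice.

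**Conclusion.** The point holds as an ambiguity of interpretation. The same variable families are outcomes of activity in the Objectives and secondary outcomes, and confounders in the prognosis model. The text supports both roles, and neither the selection rules nor the stated timing separates them. The single fully adjusted activity odds ratio therefore cannot serve as the overall effect for Objectives 1 and 2, and a null value would not show that activity does not matter.

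The document does not establish that the planned model is wrong, that its odds ratio is biased toward 1, or how large any attenuation would be. The losses shown (about 10% to 44% of the log odds ratio, or an odds ratio of 2.2 falling to 1.6 when half the effect is mediated) rest on assumed effect sizes, mediator shift or correlation, event rate and mediated share. They show that the issue could matter at this sample size, not that it will.

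**What to change.** In the Statistical analysis section:

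1. Restrict the psychosocial, sleep-quality and hematologic covariates to baseline values.
2. Pre-specify two activity models and report their odds ratios side by side:
   - **(a)** activity with baseline TMD clinical indices and background covariates, without psychosocial scores, sleep quality and hematologic indices;
   - **(b)** the same model plus those variables.
3. State that (a) may keep confounding by mood and sleep, and that (b) may remove mediated effect. Read the two as bracketing the activity effect. That reading assumes that residual confounding and mediation act in the same direction, as the Discussion's account suggests. It does not cover unmeasured confounding.
4. State that no effect of activity will be concluded from (b) alone.

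The wake-after-sleep-onset, sleep-efficiency and fragmentation measures from actigraphy should be assigned explicitly, most naturally with sleep quality in (b). Because (a) conditions on baseline TMD status, it describes prognosis from baseline onward, and any earlier influence of activity on baseline pain is outside it.

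Cost: one extra model on data already being collected, and two estimates to interpret instead of one.

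### No physical-activity exposure is designated in the prognosis model: the grouping uses weekly MVPA minutes, the model names energy, MET, steps and movement index, and the elimination and 10% rules have no odds ratio to refer to

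*Protocol article*

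**What the plan says.** Four parts of the protocol article use physical activity.

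- **Objectives.** The first objective concerns the long-term effect of objectively measured activity and sleep duration. The second concerns treatment response, by "determining the cut-off value for physical activity that affects treatment prognosis". Neither fixes a metric.
- **Patient grouping, MVPA criterion.** Active means "150 min or more per week engaging in moderate-intensity physical activity or 75 min or more per week engaging in vigorous-intensity physical activity"; Inactive means below both limits. The scale is minutes per week above an intensity level. The section names no instrument. Study outcomes assigns the amount of activity to the ActiGraph, measured at baseline only.
- **Sample size calculation.** The estimate is "based on the primary outcome of physical activity level measured in minutes and 77.8 min as between-group difference". Neither the intensity of those minutes, nor a per-day or per-week base, nor the two groups compared is stated.
- **Statistical analysis.** Logistic regression is to identify factors associated with worse long-term prognosis. The independent variables are the listed potential confounders together with "actigraphy data such as the amount of energy consumption per day, metabolic equivalent of task, steps count, sleep time, wake after sleep onset", followed by further sleep indices and a movement index. MVPA, activity minutes and the Active/Inactive group do not appear anywhere in this section. All factors are entered, then removed one at a time, highest p-value first. A confounder with p between 0.250 and 0.300 stays if it shifts the odds ratio by more than 10%.

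**The concern.** The study is about activity and prognosis, so a reader of the analysis section should be able to point to the term whose coefficient answers that question. Here there is none. Activity is represented by several indices of equal standing with the confounders, and the index that defines the study's own groups is not among those named.

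Three things are at stake. The activity effect may be eliminated, because nothing expressly holds any activity term in the model. It may be diluted, because each index is adjusted for the others. Or it may survive as steps, MET or energy, so that the adjusted result and any cut-off cannot be set beside the Active/Inactive comparison. With no exposure named in advance, the choice of which activity result to report also falls after the data are seen.

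**Working it through.** **1. The scales side by side**

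| Section | Activity variable | Unit and time base |
|---|---|---|
| Patient grouping | moderate and vigorous activity time | minutes per week, limits 150 and 75 |
| Sample size calculation | physical activity level | minutes, time base not stated |
| Statistical analysis, logistic model | energy consumption, MET, steps, movement index | energy is per day; no base given for the others |
| Objectives, cut-off | physical activity | not stated |

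**2. The plan's own figure.** The total of 214 (107 per group) cannot be reproduced, because no standard deviation is given. Solving backwards, two-sided at 0.05 with 90% power and 20% dropout taken off 107 (107 × 0.8 = 85.6 evaluable per group):

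SD = 77.8 / [(1.960 + 1.282) × √(2/85.6)] = 157.0 min.

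This is circular and confirms nothing. The missing SD is a separate matter, and the present point changes no sample-size figure.

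**3. Why the time base matters.** If 77.8 min is per week, it is 77.8/150 = 52% of the weekly moderate-activity limit. If it is per day, it is 77.8 × 7 = 544.6 min per week, or 544.6/150 = 3.6 times that limit. The text allows either, so the sizing scale cannot be matched to the grouping scale.

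**4. Applying the model rules.** Suppose energy, MET and steps are in the model and a confounder has p = 0.27. The rule asks whether removing it moves the odds ratio by more than 10%. There are then at least three activity odds ratios, plus those for sleep, and they need not agree. The rule therefore has no unique answer. Nor does the text exempt any activity term from removal.

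**5. Illustration of size.** The documents give no correlation r between activity measures, so 0.5 to 0.9 is assumed. None of these figures is a property of this study.

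- *Mutual adjustment.* With two indices correlated r in one model, each standard error grows by about 1/√(1 − r²).
- *Different classification.* If MVPA and another index were each split at the median under a bivariate normal, the share classified differently is arccos(r)/π.
- *Proxy.* If prognosis depended on MVPA, an analysis on MVPA had 90% power, and a single proxy were used instead, power = Φ(3.242r − 1.960).

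| r | SE factor | Classified differently (of 214) | Power with one proxy |
|---|---|---|---|
| 0.9 | 2.29 | 14.4% (31) | 83.1% |
| 0.8 | 1.67 | 20.5% (44) | 73.7% |
| 0.7 | 1.40 | 25.3% (54) | 62.1% |
| 0.6 | 1.25 | 29.5% (63) | 49.4% |
| 0.5 | 1.15 | 33.3% (71) | 36.7% |

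Limits: the actual grouping is the two-part 150/75-minute rule, not a median split. The 90% in Sample size calculation refers to a difference in activity minutes, not to this logistic model. Several indices entered together would recover part of the loss in the last column.

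**The case against.** The strongest reply is that the list of actigraphy variables is explicitly illustrative. MVPA minutes are actigraphy data, so they already fall within the model inputs, and a full variable list is what a journal article leaves to a fuller document. The abstract also announces correlations between activity indices, in the plural, and long-term prognosis. Using groups for between-group tests and several indices for prognosis is a legitimate division of work.

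Much of this stands. A reader might infer the following, and the documents do not support it:

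- *That MVPA is excluded from the model.* It is only not named.
- *That the main or only prognosis analysis omits MVPA.* The article labels no analysis as main. It also plans Kaplan–Meier and Cox models for prognostic value, and the activity groups may enter the unspecified between-group tests.
- *That grouping and sizing rest on the same variable.* Sample size calculation never mentions MVPA or weeks, treats activity as an outcome, and could refer to the disability groups.
- *That the Discussion ranks MVPA above other measures for this study.* Its remark concerns C-reactive protein.
- *That the study loses a known amount of power.* The figures above rest on assumed correlations and a borrowed 90%.

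It can also be argued that elimination applies only to confounders and not to the actigraphy terms. The text speaks of factors being added and discarded and does not separate the two. Even on that reading, several activity odds ratios remain and the 10% rule does not choose among them. The open list does not answer this either: adding MVPA to it would add one more overlapping index and still designate no exposure.

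**Conclusion.** The point holds as a badly fixed rule, not as a contradiction. The analysis section sets out variables, an elimination sequence and a change-in-OR criterion, yet designates no activity exposure for them to serve. Followed as written, it can lose the activity effect, adjust activity for itself, or return a cut-off that cannot be read against the 150/75-minute groups. This bears directly on the first two objectives.

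Its size cannot be derived from the documents. The tabulated values show only that the consequence ranges from modest to substantial over plausible correlations. The conclusion does not depend on them, nor on reading the 77.8 min as MVPA. The preference for MVPA as the exposure rests on its being the scale that already defines the study's groups, not on evidence that it predicts prognosis better.

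**What to change.** In Statistical analysis:

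1. Name one primary activity exposure consistent with the grouping: weekly MVPA minutes from the baseline actigraphy. Confirm in Patient grouping that the ActiGraph is the source.
2. Keep that term in the prognosis model at every step, exempt from p-value elimination.
3. State that the 10% rule refers to the change in this term's odds ratio.
4. Report the cut-off for the second objective on this scale.
5. Fit energy consumption, MET and steps one at a time, each in a separate supportive model. Do the same for movement index if it is meant as an activity measure.

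In Sample size calculation, state which minutes the 77.8 refers to, and whether it is per day or per week.

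The cost is wording. No new data are needed, provided the groups are derived from actigraphy, since MVPA minutes must then be computed anyway. The downside is that energy, MET and steps become supportive rather than main results.
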